### Study variables

Sociodemographic information such as age, skin phototype [classified by the Fitzpatrick scale], weight and height. The primary outcome is orofacial pain, and the secondary outcomes are oxygen saturation, blood pressure, heart rate, local temperature, blood lactate levels, and hemoglobin levels. In addition to demographic, anthropometric, and hemodynamic variables, the penetrated energy will be quantified using a power meter, and information from orofacial pain and headache symptom questionnaires will be analyzed.

### Randomization

The participants will be informed that they will be randomly assigned to one of the four study groups that will be compared. To allocate the participants to the groups, a stratification process will be carried out based on the answers to the questionnaires and the presence of orofacial pain symptoms and the presence of headache symptoms will be considered strata. Stratification will be carried out to balance the allocation of participants in each group according to stratum.

After stratification, participants will be randomized in a 1:1:1:1 ratio into the 4 groups. The randomization list will be generated by an independent researcher in random blocks of four, electronically via the ramdomizer.org website and kept in opaque envelopes. The allocation will only be revealed to the operating researcher at the time of the intervention. A study team member, separate from the researcher who will administer the intervention, will follow the random allocation sequence to assign participants to a study group and prepare study equipment and materials. Eligible participants will be randomly assigned to Group 1—Local Photobiomodulation, Group 2—Vascular Photobiomodulation, Group 3—Placebo Local Photobiomodulation, or Group 4—Placebo Vascular Photobiomodulation using stratified block randomization generated by the study statistician.

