#### Group 3 –Placebo local photobiomodulation

Group 3 will undergo the same procedures described for Group 1, but the equipment will emit only the sound signal, exactly like the equipment used in Group 1, without the emission of laser light.

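### A single block size of four for four arms makes the last allocation of each complete block deducible, and the text separately tells the treating researcher who is active and who is sham.

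*Protocol article*

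**What the plan says.** The Randomization section of the protocol article fixes these rules:

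- Ratio and arms: "participants will be randomized in a 1:1:1:1 ratio into the 4 groups". The groups are local and vascular photobiomodulation and a placebo version of each.
- Strata: "the presence of orofacial pain symptoms and the presence of headache symptoms will be considered strata".
- Blocks: "The randomization list will be generated by an independent researcher in random blocks of four".
- Concealment: the list is produced "electronically via the ramdomizer.org website and kept in opaque envelopes".
- Assignment: "A study team member, separate from the researcher who will administer the intervention, will follow the random allocation sequence", and this person also prepares the equipment.
- Disclosure: "The allocation will only be revealed to the operating researcher at the time of the intervention".

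For the local placebo group, "the equipment will emit only the sound signal, exactly like the equipment used in Group 1, without the emission of laser light". The vascular placebo is described in the same way. The Group 1 and Group 2 sections limit those present at application to the participant, the treating researcher and the guardian. The second paragraph under Hemoglobin level has heart rate, blood pressure, oxygen saturation, light transmission and temperature collected during application. Under Light transmission, a power-meter sensor sits inside the cheek while the researcher irradiates the masseter. Study variables names orofacial pain as the primary outcome. The article nowhere says that the operator is masked or that devices are coded.

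**The concern.** There are two distinct problems.

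The first concerns prediction before allocation. Four is the smallest block that can hold four arms equally, so it is the most predictable choice, and the size is published in the article. Opaque envelopes protect the next envelope. They do not stop someone from deducing its content from those already opened, and the operator learns every allocation. If such a person could influence who is enrolled or when, the comparison of groups could be biased at entry.

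The second concerns knowledge after allocation. The groups are active and placebo versions of each route, so revealing the group also reveals active or sham. The operator must know the route (face and neck, or wrist) but does not need to know whether the device emits. On the text, the operator is the only staff member present when several secondary outcomes are recorded, and is with participants aged 7 to 19 over four sessions in a trial of pain. A sham with the same sound can mask the participant, but that protection is weaker when the person giving the treatment knows the assignment.

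**Working it through.** The plan gives no figure to reproduce: 180 is a convenience sample, and the article states no predictability measure.

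**Inputs.** Four arms, 1:1:1:1, one block size of four, and strata from two symptoms (Randomization); N = 180 (Sample). Two symptoms give at most four strata. Entry requires at least one symptom, so three non-empty strata is likely, but that is an assumption.

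**Guessing the arm.** Within a block each arm occurs once. At position k, 5 − k arms remain, all equally likely, so the chance of a correct guess is 1/(5 − k): 1/4, 1/3, 1/2, 1.

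- Sum: 1/4 + 1/3 + 1/2 + 1 = 25/12 = 2.083 correct per block.
- Rate: 2.083/4 = 52.1%, against 25% under simple randomization.
- The fourth position is certain in all 4! = 24 orderings.

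**Guessing active versus sham.** Each block has two of each.

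- Position 1: 1/2.
- Position 2: 2/3 (two of the three remaining are of the other kind).
- Position 3: with probability 1/3 the first two were the same kind, and the third is then certain; otherwise it is a coin toss. So 1/3 × 1 + 2/3 × 1/2 = 2/3.
- Position 4: 1.
- Rate: (1/2 + 2/3 + 2/3 + 1)/4 = 2.833/4 = 70.8%, against 50%.

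**Number of certain allocations.** With one stream, 180/4 = 45 complete blocks, hence 45 certain allocations (25%). With S strata, each may end with 0 to 3 participants in an unfinished block, and these remainders must sum to a multiple of 4.

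- S = 2: largest possible sum 4, so at least (180 − 4)/4 = 44.
- S = 3: largest 8, so at least (180 − 8)/4 = 43.
- S = 4: largest 12, so at least (180 − 12)/4 = 42.

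**Effect of other block sizes.** The alternative sizes are illustrative. The varying schemes were simulated over 180 allocations in one stream (60 to 100 runs), with sizes equally likely and a guesser who knows the possible sizes but not the current one and updates by Bayes' rule.

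| Scheme | Correct arm guesses | Certain allocations |
|---|---|---|
| Fixed 4 | 52.1% (exact) | 25% |
| 4 or 8 | 48.9% | 7.6% |
| 4, 8 or 12 | 46.8% | 3.5% |
| 8 or 12 | 45.1% | 4.7% |

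A simpler guesser who names the arm used least so far, with an assumed 60 participants per stratum and 1,500 runs, gives 45.9% for 4, 8 or 12. So the guess rate is about 46-47%. Certain allocations fall from 45 to about 6 (0.035 × 180 = 6.3). The main gain is the loss of certainty; the average guess rate changes little.

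**Masking.** Block size does not affect whether the operator is masked. That depends on who is told the allocation and on what the operator can see. A sham that emits no light should give no transmitted signal on the meter, and the local laser is described as red, so its absence may be visible.

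**The case against.** The strongest reply is that the section already has opaque envelopes, disclosure only at the time of the intervention, and a separate person who assigns participants. Predicting a fourth slot does harm only if the predictor controls eligibility or timing, and knows each participant's stratum and the block size. No section says that the operator recruits, or who sees the questionnaires that define the strata. This stands. A reader might infer that enrolment is open to manipulation; the article supports only that allocations are deducible, and the enrolment harm is conditional.

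A reader might also infer that the unmasked operator scores the pain outcome. The article does not say who administers the questionnaires, and a condensed article may leave that to the full protocol, so it is not part of this point.

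It can also be said that coding the devices would not mask the operator in the local groups, because of the power meter and the missing light. This stands too. It limits and extends the remedy, but it does not justify telling the operator outright.

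Random blocks may mean randomly permuted blocks. That is a fair reading, but the size remains four; no reading yields varying sizes.

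Finally, the section credits the list to an independent researcher and later describes it as "using stratified block randomization generated by the study statistician". A reader might infer a contradiction, but one person could fill both roles. It is a wording matter with no bearing on predictability or masking.

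**Conclusion.** The point holds in two limited parts. First, a single block size of four makes the fourth allocation of each complete block certain: at most 45 of 180, and 42 to 45 with up to four strata. Expected correct guesses are 52% against 25% for the arm and 71% against 50% for active versus sham. This assumes someone who knows the block size and tracks allocations within each stratum. Bias at entry requires the further, unstated condition that this person, or someone this person informs, influences enrolment or timing.

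Second, whatever the block size, the text unmasks the operator to active or sham when nothing in the procedure requires it. The operator is the only staff member stated to be present while heart rate, blood pressure, oxygen saturation and temperature are collected. The documents allow no estimate of the resulting bias in these measurements or in pain. Both parts concern stated rules that can be improved at low cost.

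**What to change.** 1. Generate the list with randomly varying block sizes within each stratum, for example 4, 8 and 12, and keep the sizes from everyone who recruits or treats.
2. Have the team member who already prepares the equipment set active or sham by code, and tell the operator only the route. Replace the sentence on disclosure to the operating researcher accordingly.
3. Hide the power-meter display from the operator, or have that same team member log it. If that person must enter the room, adjust the Group 1 and Group 2 text on who is present.
4. State that operator masking in the local groups may be incomplete, because the sham emits no light.

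The cost is a regenerated list, revised wording and minor changes to session logistics. The statistical downside is a slightly larger possible imbalance within small strata: two arms can differ by at most 1 within an unfinished block of four, but by up to 3 within an unfinished block of twelve (12/4 = 3 places per arm).

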### Data collection

#### Blood lactate

Blood lactate will be collected before treatment, immediately after the first session, and after the last session. The collection will be done at the distal phalanx of the middle finger [one drop of blood], after local hygiene with 70% alcohol. For puncture, the researcher will use surgical gloves and disposable lancets. The blood sample will be analyzed by LACTATE DETECT TD-4261 [Eco Diagnóstica, Nova Lima, MG, Brazil] [10].

#### Hemoglobin level

The hemoglobin level will be analyzed before treatment, immediately after the first session, and after the last session. The same puncture performed for lactate collection will be used for hemoglobin analysis. The blood drop will be analyzed by the Hb Analyzer ECO CARE [Eco Diagnóstica, Nova Lima, MG, Brazil].

The variables of heart rate, blood pressure, oxygen saturation, light transmission, and local temperature will be collected during the application of photobiomodulation, which will take place in a private setting in the dental office of the Health Sector Nucleus of the Teaching Center. The Handheld–Vital Sign Monitor will be used for collecting these variables.

#### Light transmission

The SPER Scientific Pocket Laser Power Meter device [Scottsdale, AZ, USA] will be used. Light transmission will be assessed through the index finger and cheek [masseter] of each participant. The sensor of the equipment will be positioned on the inner region of the cheek at the same time the researcher is applying the laser on the masseter region [2 points].

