### Sample

Individuals between 7 and 19 years of age with orofacial pain post-covid-19 will be invited to participate in the study. A convenience sample was chosen, totaling 180. Given the lack of definitive studies for sample size calculation regarding persistent COVID-19 symptoms, a convenience sample was used. Participants were chosen based on reported symptoms and inclusion criteria at the university outpatient clinic. This approach was necessary due to the evolving nature of post-COVID-19 symptomatology, which currently prevents standardized sample size determination.

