### Interventions

#### Group 1 –Local photobiomodulation

The treatment will be administered over 2 weeks, totaling 4 sessions [2 sessions per week] with an average duration of 6 minutes per session.

Participants will be positioned in a clinical chair for the application of photobiomodulation. The interventions will be conducted by a trained professional. Group 1 will receive photobiomodulation using the Therapy EC–DMC device, with a red wavelength of 660 nm and power of 100 mW, properly calibrated, delivering 6J per point [60 seconds] at 2 points in the masseter muscle region, 1 point in the left temporal muscle,1 point in the right temporal muscle, 1 point in the left trapezius muscle in the cervical region, 1 point in the right trapezius muscle. The total application time will be 4 minutes per session.

At the time of application, only the participant receiving the treatment, the researcher responsible for the treatment, and the guardian will be present. Everyone will wear specific goggles for eye protection. The equipment’s tip will be disinfected with 70% alcohol and covered with disposable transparent plastic [PVC] to prevent cross-contamination, while the facial area to be irradiated will be cleaned with a 0.2% Chlorhexidine solution. During the applications, the participant will remain seated, with the Frankfurt plane parallel to the ground. Energy penetration will be analyzed at one of the points on the masseter muscle.

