#### Group 2 –Vascular photobiomodulation

Vascular Photobiomodulation [VBMP] will be applied using the same device, with an infra-red wavelength of 808 nm and 100 mW, directing the light beam to the radial artery region for 10 minutes per session.

The participant will be seated in a comfortable chair with lateral support for resting their arms during the application. At the time of application, only the participant receiving the treatment, the researcher responsible for the treatment, and the guardian will be present. Everyone will wear specific goggles for eye protection. The active part of the bracelet will be covered with disposable transparent plastic [PVC] to prevent cross-contamination, and for hygiene reasons, the area to be irradiated will be pre-cleaned with a 0.2% Chlorhexidine solution. During the applications, the participant will remain seated, with the Frankfurt plane parallel to the ground. A new treatment method will be administered for 2 weeks, totaling 4 sessions [2 sessions per week] with an average duration of 10 minutes per session.

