#### Monte Carlo simulation

The Monte Carlo technique will be employed to simulate the fluence profile, energy deposited in different tissue layers of the cheek and index finger, and transmittance, using light of wavelengths 660 nm and 808 nm. In an initial phase, a Monte Carlo model will be developed, considering the morphological structure of the tissues to be treated, approximating their structure to a planar and laminar model consisting of four layers: epidermis, dermis, subcutaneous fat, and muscle [15].

The thicknesses of each layer will be obtained from the literature, and their values will be varied in predefined intervals consistent with literature findings for different age groups and BMI values. The optical properties of each layer, including absorption and scattering coefficients, anisotropy coefficient, and refractive index, will be gathered from bibliographic research, considering the expected variability for the sample under study.

A model for the absorption coefficient will be used, accounting for blood content in each layer, blood oxygen saturation level, as well as fractions of fat, melanin, and water in each tissue layer. Based on the preliminary study, a database will be established aiming to establish a relationship between energy deposited in tissues and different anthropometric characteristics [13, 16].

Special attention will be given to the relationship between energy deposited in the epidermis and muscle, to establish a compromise between safety limits and treatment effectiveness. Simulated transmittance values will be subsequently compared with values measured in volunteers, considering measurements of tissue thickness by ultrasound, skin type, BMI, and blood saturation levels. A computational implementation of the tissue optical model and the Monte Carlo simulation model will be developed based on Marti et al.’s MCMatlab code, available online [https://github.com/ankrh/MCmatlab], using Matlab® software, version 2022.

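### Light transmission is to be read in every participant during treatment, but only Group 1 has a beam at a measured site (cheek, 660 nm), so most of the planned model validation has no data source

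*Protocol article*

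**What the plan says.** All references are to the protocol article.

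- **Who and where** (Light transmission): "Light transmission will be assessed through the index finger and cheek [masseter] of each participant". For the cheek, the power-meter sensor sits inside the mouth while the laser is held over the masseter.
- **When** (Hemoglobin level, second paragraph): "light transmission, and local temperature will be collected during the application of photobiomodulation".
- **Group 1**: 660 nm at six points, two of them on the masseter, the others temporal and trapezius. The section adds: "Energy penetration will be analyzed at one of the points on the masseter muscle".
- **Group 2**: 808 nm, "directing the light beam to the radial artery region for 10 minutes per session".
- **Groups 3 and 4**: the equipment gives its sound signal "without the emission of laser light".
- **Use of the readings** (Monte Carlo simulation): the simulation covers "energy deposited in different tissue layers of the cheek and index finger, and transmittance, using light of wavelengths 660 nm and 808 nm", and simulated transmittance is then compared with the measured values.
- **Aim** (Abstract, Methods): validation of the dosimetry model for local and for systemic application.
- **Size** (Sample; Randomization): "A convenience sample was chosen, totaling 180", and "participants will be randomized in a 1:1:1:1 ratio into the 4 groups".

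**The concern.** The comparison of measured with simulated transmittance is how the study's main objective is to be met. A transmission reading needs light entering the tissue at the measured site. In three of the four arms the assigned treatment puts no light on the cheek, and in no arm does it put light on the finger. Staff who follow the text literally would record zeros or nothing in most participants.

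The text can be followed for every participant only by applying real light outside the assigned treatment. The article describes no such step. Done during sessions, it would put active light on a Group 1 treatment site in the vascular and placebo arms while the primary outcome, orofacial pain, is still being accrued.

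Both routes have a cost, and the text does not choose between them. Transmission readings missed during the trial cannot be recovered later.

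**Working it through.** **Step 1. Is there a beam at each measured site?** The simulated site and wavelength combinations are set against the treatment each group receives.

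| Site and wavelength | Group 1 | Group 2 | Group 3 | Group 4 |
|---|---|---|---|---|
| Cheek, 660 nm | yes | no (beam at wrist, 808 nm) | no light | no light |
| Cheek, 808 nm | no (660 nm only) | no (beam at wrist) | no light | no light |
| Finger, 660 nm | no (finger not a treatment point) | no | no light | no light |
| Finger, 808 nm | no | no (beam at wrist) | no light | no light |

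One of the four combinations has a light source, and in one group only. The radial artery, where the whole vascular dose is delivered, appears neither among the simulated sites nor among the measured ones.

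**Step 2. Number of participants.** The 180 is declared a convenience sample, so there is no sample-size calculation to reproduce. With equal allocation, 180 / 4 = 45 per group.

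- Cheek, 660 nm: about 45 of 180 (45 / 180 = 25%).
- Cheek, 808 nm: 0 of 180.
- Finger, either wavelength: 0 of 180.

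**Step 3. Exposure if everyone is read with real light during sessions.** The energies in Table 1 reproduce: 6 J × 6 points = 36 J per local session, and × 4 sessions = 144 J; for the vascular arm 0.1 W × 600 s = 60 J, and × 4 = 240 J.

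The article gives no reading time, so a range is assumed. Energy = power × time × points, with 0.1 W and two masseter points:

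- 1 s per point: 0.1 × 1 × 2 = 0.2 J; 0.2 / 36 = 0.6% of a local session.
- 10 s per point: 0.1 × 10 × 2 = 2 J; 2 / 36 = 5.6%.
- 60 s per point: 0.1 × 60 × 2 = 12 J; 12 / 36 = 33%.

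This exposure would fall on Group 2 at the cheek as well as on the placebo arms.

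**The case against.** The strongest reply is that a separate measurement step was intended and dropped when the article was condensed. Measuring a finger that nobody treats points that way, and Group 2 is said to use the same device as Group 1, so both wavelengths would be available. This is plausible, but it does not resolve the conflict: the text places the readings during application and ties the cheek reading to the laser being applied to the masseter. Nor does the mention of volunteers in the Monte Carlo section indicate a separate sample, since Patient and public involvement uses that word for trial participants.

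Several stronger readings are tempting but not supported:

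- **Unblinding.** A reader might infer that a zero on the meter reveals the allocation. Under Randomization the operating researcher already learns it at the intervention. A participant or guardian would have to see and interpret the meter, which the article does not describe.
- **Two points against one.** Light transmission mentions two masseter points and the Group 1 section one. The two may describe where the laser is applied and the one where penetration is read, so the statements can be compatible.
- **Heavy contamination of placebo.** Totals of 24 J (one point) or 48 J (two points) over the trial, 17% or 33% of 144 J, require full 60 s readings at all four sessions. Nothing says so, and a 1 s reading may be trivial.
- **45 is too few.** The approximate 95% half-width of a limit of agreement, 1.96 × √(3/n), is 0.51 SD at n = 45 and 0.25 SD at n = 180. The article plans no such analysis and sets no precision target, and the formula assumes one reading per participant. It does not show that 45 is inadequate.
- **Incomplete modelling as an error in itself.** Simulating only the cheek and finger, and taking ultrasound over the masseter only, are choices of scope. What stands is that the claim for systemic application has no modelled or measured irradiation site.

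**Conclusion.** The inconsistency holds and affects the stated objective. Under the treatments as described, in-vivo data can be obtained for one of four simulated site and wavelength combinations, in about 45 of 180 participants (25%), and not at all for 808 nm, the finger or the vascular site. This rests on two assumptions: that readings use only the light of the assigned treatment, as the text says, and that allocation comes out equal.

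The other route, real light for everyone during sessions, would give Groups 2 to 4 unassigned exposure of between 0.6% and 33% of a local session's energy. That range rests on assumed reading times of 1 to 60 s at two points and on pain assessment not yet being complete at that time. Whether it would matter for the pain comparison cannot be judged until the reading time is stated. The feasibility conflict alone requires correction, whatever the exposure.

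**What to change.** Reconcile the sections on Light transmission, Hemoglobin level (second paragraph), the four intervention groups and Monte Carlo simulation. State in which groups, at which sites and wavelengths, at how many points and when transmission is read, and the resulting validation sample size. Two options are workable:

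- **(a) Separate measurement step.** Take finger and cheek readings at both wavelengths in all participants, in a brief step after the last pain assessment and blood sample. Any treatment-time reading is kept in Group 1 only. State the measurement exposure and obtain ethics approval for it, since participants are aged 7 to 19. The cost is an added step and a brief light exposure in the placebo and vascular arms once their outcomes are complete. In return, up to 180 participants can contribute, and the pain comparison is protected.
- **(b) Narrower claim.** State that in-vivo validation rests on about 45 Group 1 participants, for the cheek at 660 nm, and drop the validation claim for 808 nm, the finger and the vascular route. This costs only wording, but gives up a large part of the stated objective.

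In either case, limit the in-vivo validation claim to the sites actually measured. Option (a) still provides no reading at the radial artery.

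### Light transmission is to be read at the finger and cheek of every participant, but as treatment is written only Group 1 (about 45 of 180) has light at the cheek, at 660 nm, and no group has light at the finger

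*Protocol article*

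**What the plan says.** Two sections govern the measurement. Light transmission sets who and where: "Light transmission will be assessed through the index finger and cheek [masseter] of each participant". It places the sensor inside the cheek and takes the reading "at the same time the researcher is applying the laser on the masseter region [2 points". The second paragraph under Hemoglobin level sets the timing: "light transmission, and local temperature will be collected during the application of photobiomodulation".

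The Interventions sections set where light is present:

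- **Group 1** is treated at 660 nm at masseter, temporal and trapezius points. Its section adds: "Energy penetration will be analyzed at one of the points on the masseter muscle".
- **Group 2** is treated at 808 nm, "directing the light beam to the radial artery region for 10 minutes per session".
- **Group 3** follows Group 1's procedures with a device that gives only the sound, "exactly like the equipment used in Group 1, without the emission of laser light".
- **Group 4** follows Group 2's procedures on the same sham terms.

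The Monte Carlo simulation section simulates cheek and index finger at both 660 nm and 808 nm and compares simulated transmittance with values measured in volunteers. The abstract names that comparison as the means of validating the model.

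**The concern.** A transmission reading needs light entering the tissue at the site where the sensor sits. The measurement sections assume this for every participant at two sites. The intervention sections supply it in one arm at one of those sites. Two ways of carrying out the plan remain, and each breaks something the article says.

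- **Readings come from the randomised applications.** Most participants then have no usable reading, and the only described test of the dosimetry model rests on one arm, one site and one wavelength.
- **Everyone is irradiated for the reading.** Participants in the sham arms then receive laser light, against the definition of those arms. Vascular participants receive light at a Group 1 treatment site. If this happens before pain is assessed, it can blur the active-versus-placebo contrast in the primary outcome.

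Neither missing readings nor a blurred contrast can be repaired at analysis, so the choice has to be made before data are collected.

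**Working it through.** **Inputs.** Total sample: "A convenience sample was chosen, totaling 180" (Sample). Allocation: "participants will be randomized in a 1:1:1:1 ratio into the 4 groups" (Randomization). Sites, wavelengths and emission by arm: the four Interventions sections and Table 1. Simulated sites and wavelengths: Monte Carlo simulation. The 180 has no power calculation behind it, so there is no sample-size figure to reproduce.

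**Step 1, count of usable readings with treatment delivered as written.** Per arm: 180/4 = 45. Usable readings = 45 × number of arms with light of that wavelength at that site.

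| Site | Wavelength | Arms with light | Participants |
|---|---|---|---|
| Cheek | 660 nm | 1 (Group 1) | 45 (25% of 180) |
| Cheek | 808 nm | 0 | 0 |
| Index finger | 660 nm | 0 | 0 |
| Index finger | 808 nm | 0 | 0 |

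Three of the four simulated combinations have no in vivo counterpart. The 45 is before the exclusions under Discontinuation or interruption criteria and before any dropout, for which no rate is given.

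**Step 2, what 45 rather than 180 means for precision (illustration only).** The article names no agreement statistic and no target precision. Assuming one simulated-minus-measured difference per person with standard deviation SD:

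- 95% CI half-width of a limit of agreement ≈ 1.96 × √(3/n) SD: 0.51 SD at n = 45, 0.25 SD at n = 180.
- 95% CI half-width of the mean difference = 1.96/√n SD: 0.29 SD at n = 45, 0.15 SD at n = 180.

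A quarter of the people doubles the width of either interval.

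**Step 3, exposure if everyone is irradiated for the reading.** People exposed at the cheek outside Group 1: 3 × 45 = 135, of whom 2 × 45 = 90 are in the sham arms. The energy depends on a duration that the article does not state. At the Group 1 treatment setting, 0.1 W × 60 s = 6 J per point:

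- One masseter point (Group 1 section): 6 J.
- Two masseter points (Light transmission section): 12 J.
- A brief reading, assumed here to last 5 s at one point: 0.1 W × 5 s = 0.5 J.

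For scale, a Group 1 session is 6 × 6 = 36 J and the course is 4 × 36 = 144 J, which matches Table 1. So 12 J is one third of a session and about 8% of the course (12/144).

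**The case against.** The strongest reply is that the timing is looser than it looks. The sentence that times light transmission to the application also assigns it to the vital-sign monitor, whereas the Light transmission section uses a laser power meter. The abstract's list of variables collected during application omits light transmission. The simultaneity sentence covers the cheek only, so the finger's timing rests on one loosely worded sentence. The SPIRIT schedule is not shown, and the full protocol may describe a separate measurement exposure. The Group 1 section mentions energy penetration for that arm, so the reference to every participant may simply be careless wording.

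These points weaken any claim about what will happen in the clinic. They do not remove the conflict. No separate exposure is described, and if there were one it would still put active light on Groups 2 to 4. A schedule cannot supply light in a sham arm or at an untreated finger.

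Three limits on size do stand:

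- The article states no validation sample size. A reader might infer that it claims 180 and that the claim is false. In fact 180 is the trial total, and 180 readings only follow from the wording on who is measured.
- A reader might infer that 45 is too few. With no criterion stated, the figures show less precision, not inadequacy. Group 1 has four sessions and one or two masseter points, so repeated readings could reduce measurement noise, though they add no people.
- A reader might infer that the sham arms will receive 12 J. That is a worst case, and no effect of such an exposure on pain is shown.

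**Conclusion.** The point holds as an internal contradiction. Under the treatments as written, measured transmittance is available for the cheek at 660 nm in about 45 of 180 participants before exclusions. It is available in none for the finger at either wavelength or for the cheek at 808 nm. The only route to readings in everyone is active light in Groups 2 to 4, which conflicts with the sham definitions and could affect the pain contrast if it precedes the outcome.

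The count of 45 rests on the stated 1:1:1:1 allocation and on there being no separate measurement exposure. The 6 to 12 J range assumes the treatment setting for a full 60 s, and a shorter reading gives less. The documents do not support saying that contamination will occur or that the validation is bound to fail. They show that the plan does not yet say which of two incompatible procedures applies, on the element the study exists to test.

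**What to change.** Reconcile Light transmission, the second paragraph of Hemoglobin level, the four Interventions sections and Monte Carlo simulation on five items: who is measured, at which site, at which wavelength, at how many masseter points (Light transmission has two, the Group 1 section one), and when. Then choose one route.

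- **(a) Measure everyone, after outcomes.** Take the cheek and finger reading that Light transmission already prescribes once in all participants, after their last pain and blood assessment. State the wavelength or wavelengths and the duration. Record oxygen saturation at the same time, because the simulation comparison uses it. Cost: a few minutes at the last visit, plus consent, assent and ethics-committee notification, since sham participants aged 7 to 19 would receive a laser exposure.
- **(b) Restrict to Group 1.** Limit the reading to the cheek in Group 1, state about 45 participants (cheek, 660 nm) as the validation sample, and report the finger and 808 nm results as simulation only. Cost: wording, and a narrower validation claim in the abstract and the Monte Carlo simulation section.
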